#### Statistical Analyses

Descriptive statistics including means, standard deviations, medians, interquartile ranges and frequency distributions will be used to summarize the data. For univariate analyses, we will use the Chi-square test (alternatively, Fisher's exact test when the expected value is ≤ 5) and Student's t-test (alternatively, the Mann-Whitney U-test, if normality assumptions are not satisfied) for binary and continuous outcomes, respectively. We will evaluate the percentage of (i) hours off-protocol and (ii) daily SAS scores < 2 or > 5 (or RASS equivalent) by treatment group. Compliance will be considered acceptable if ≥ 75% [that is; protocol violations (off protocol hours without meeting criteria to return to/remain on an alternate mode of mechanical ventilation) or SAS scores < 2 or > 5 (equivalent RASS -4 < or > +1) occur < 25% of the time]. SBT compliance will be considered acceptable if ≥ 75% of SBT opportunities are realized. We will compare average Likert scale scores based on clinician group and the weaning strategy utilized using Analysis of Variance (ANOVA). We will compare time to successful extubation and death between groups using time-to-event analysis with censoring of deaths and application of the log-rank test. We will consider p-values ≤ 0.05 to be statistically significant.

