## Methods

### Study Design

A pilot RCT is currently underway at 8 adult ICUs across Canada in collaboration with the Canadian Critical Care Trials Group. Ethics approval for the study was obtained from the Research Ethics Board (REB) at St Michael's hospital and the REBs of participating centres. Figure 1 provides an overview of the study.

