#### Sample Size

Estimates are not available to allow precise sample size estimation of the primary outcome for the multicentre pilot RCT. To ensure that the study protocols are easy to follow before engaging in a definitive weaning RCT, we estimate that a total of 90 patients (ideally approximately 11-12 patients per site) are required to assess protocol compliance. To ensure that all centres gain some experience with both protocols, we set a maximum site enrolment of 35 patients.	

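### The 75% compliance verdict is a bare point estimate with an ambiguous time denominator, and the 35-patient site cap cannot ensure that every centre gains experience

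*Protocol article*

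**What the plan says.** Study Outcomes makes compliance with the weaning and sedation protocols the primary outcome. Statistical Analyses states the measure, "We will evaluate the percentage of (i) hours off-protocol and (ii) daily SAS scores < 2 or > 5" by treatment group, and the rule: "Compliance will be considered acceptable if ≥ 75" per cent. A bracket explains that violations must take up less than a quarter of the time, and that a violation is an off-protocol hour when no criterion for an alternate mode was met. Those criteria are listed under Criteria to suspend weaning protocols. SBT compliance has its own 75% mark, taken over SBT opportunities.

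Sample Size says "Estimates are not available to allow precise sample size estimation of the primary outcome", then that "a total of 90 patients (ideally approximately 11-12 patients per site) are required to assess protocol compliance". It adds: "To ensure that all centres gain some experience with both protocols, we set a maximum site enrolment of 35 patients". Study Design gives the number of centres: "A pilot RCT is currently underway at 8 adult ICUs across Canada". Under Run-in Phase, each centre had already treated one patient on each strategy before the pilot began.

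**The concern.** There are three linked weaknesses in what the article fixes.

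- **The verdict.** Acceptable or not is read off the estimate alone. With a few dozen patients per arm, a true value some points either side of 75% can land on the wrong side.
- **The denominator.** Authorised off-protocol hours are removed from the violations but not clearly from the time they are divided by. If they stay in, patients whose protocol is suspended most will tend to look most compliant.
- **The cap.** A maximum per site is given as the means of securing experience at all sites, which is a minimum.

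At stake is how far the compliance result, the only outcome with an acceptability threshold, can be trusted when a definitive trial is planned.

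**Working it through.** **Plan's own figure.** 90 / 8 = 11.25 per site, which agrees with the stated 11-12. The total of 90 cannot be reproduced, because the article says no estimates exist and gives no precision target.

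**Cap.** 90 / 35 = 2.57, so three centres suffice: 35 + 35 + 20 = 90. Two centres could supply 70 / 90 = 78%. The cap is 35 / 11.25 = 3.1 times the ideal.

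**Precision, patient as unit, 45 per arm (1:1 assumed).**
- Wilson 95% interval for 34/45 (75.6%): centre 73.5%, half-width 12.2 points, so 61.3% to 85.8%.
- Half-width at 75%: 1.96 × √(0.75 × 0.25 / 45) = 12.7 points.
- A true 70% reaches 34/45 or more with probability 0.26; a true 80% falls short with probability 0.17.
- For the lower Wilson limit to reach 75%, 40/45 (88.9%) would be needed.

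These figures treat each patient as wholly compliant or not, which is the widest case for a per-patient average before centre clustering. If patients vary continuously with SD √(ρ × 0.75 × 0.25), then ρ = 0.3 to 0.5 (assumed) gives an SD of 24 to 31 points and a half-width of 1.96 × SD / √45 = 6.9 to 8.9 points.

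**Centre clustering, all-or-nothing case.** Design effect = 1 + ICC × (Σm²/Σm − 1); ICC assumed.

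| ICC | Eight equal centres | Three centres (17.5, 17.5, 10 per arm) |
|---|---|---|
| 0.01 | 12.9 points | 13.6 points |
| 0.05 | 14.0 | 16.7 |
| 0.10 | 15.3 | 19.9 |

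**If hours are pooled.** The cited 144-patient trial (Background) had median total ventilation of 9 and 6.5 days, with 15.7% and 6.7% beyond 21 days. Under a lognormal model, log-SD = ln(21/median) / z:
- 0.847 / 1.007 = 0.84
- 1.173 / 1.499 = 0.78

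Simulating 45 durations at these values (medians 2 and 4 days, truncated at 90 days), the effective number of patients, (Σd)²/Σd², has a median of 25 to 27. The five longest stays hold 31% to 33% of the hours. With 25 effective patients and the same SDs, the half-width grows to 1.96 × SD / √25 = 9.3 to 12.0 points. In simulations at log-SD 0.8 and true mean compliance of 70%, the pooled figure passes in 16% to 23% of trials and the per-patient mean in 9% to 15%.

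**Denominator.** Let a be the share of hours authorised off protocol and v the violation hours as a share of all hours. Over all hours, compliance passes when v < 0.25. Over applicable hours it passes when v / (1 − a) < 0.25, that is, v < 0.25 × (1 − a). The two readings disagree when v lies between these limits:
- a = 10%: v from 22.5% to 25%
- a = 20%: v from 20% to 25%
- a = 30%: v from 17.5% to 25%

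The article does not give a, so these shares are assumptions.

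**The case against.** The strongest reply is that a journal article leaves the unit of analysis, intervals and clustering to a fuller document. That largely stands for the unit. A reader might infer that hours are pooled by arm, but the text says only that percentages are evaluated by treatment group. The same section lists means, SDs, medians and rank tests, which suit per-patient values. Share of time on protocol is also a legitimate quantity for a protocol meant to run continuously, and a per-patient mean gives a very short stay the same weight as a very long one. Neither is wrong.

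A reader might also infer that this one percentage decides whether the definitive trial proceeds. The article states no such rule, and Objectives adds clinician acceptance and recruitment. Nor would heavier skew than 0.78 to 0.84 be supported by the figures it cites, although those describe total ventilation and are only a proxy for weaning time.

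On the denominator, the wording is ambiguous rather than plainly wrong. On the cap, the run-in did give every centre one patient per strategy, and three centres filling the trial is the permitted extreme, not the aim.

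What the reply does not remove is what the article itself states: a verdict set on the estimate alone, a time base at odds with the SBT rule next to it, and a maximum credited with securing a minimum.

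**Conclusion.** The point holds in this limited form. Near 75% the verdict is uncertain: the interval is about 61% to 86% at 34/45 in the all-or-nothing case, narrower if compliance varies continuously between patients, and wider again with centre clustering or pooled hours. Much of this comes from having 45 patients per arm; pooling adds to it but is not the main cause. The denominator can change the verdict only when violations lie just under 25% of all hours and authorised suspensions are common. The cap arithmetic is exact and needs no assumption: within the pilot, five centres could enrol nobody.

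The sizes rest on 1:1 allocation, lognormal durations, and the ICC and between-patient variation shown.

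**What to change.** In Statistical Analyses:
- Define weaning compliance over hours when no criterion for suspending the protocol is met.
- Report a 95% interval beside each 75% verdict, by bootstrap over patients within centres.
- Show both the pooled-hours and the per-patient figure by arm, and say in advance which one is read against 75%.

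In Sample Size, do one of two things:
- Say that the cap only limits dominance by one site, and that the run-in supplied each centre's first experience of both strategies.
- Reserve a small minimum per centre with both arms represented, released after a set date. A number alone is not enough: with four places and simple 1:1 allocation (assumed), all four fall in one arm with probability 2 × 0.5⁴ = 12.5%, and at least one of eight centres misses an arm with probability 1 − 0.875⁸ = 66%.

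The analysis changes cost wording and a little programming, and the verdict will look less certain. Reserved places may slow recruitment slightly.

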### Criteria for Pressure Support Trial

We consider consented patients, who meet *the Criteria for Consent*, to undergo a PST at least once daily when they meet the following criteria:

1) intubated patient on mechanical ventilation,

2) SpO_2 _≥ 90% with FiO_2 _≤ 50% and PEEP ≤ 10 cm H_2_O,

3) no requirement for high dose vasopressors (i.e., no epinephrine or norepinephrine > 15 µg/min (or 0.2 µg/kg/min) or equivalent dose vasopressin or phenylephrine),

4) motor component of the Glasgow Coma Scale score ≥ 4 (withdraws to pain),

5) stable neurological status (no deterioration in the last 24 hrs, intact respiratory drive, and intracranial pressure < 20),

6) patient not expected to be extubated on the day of study randomization,

7) no surgery or procedure requiring sedation planned in the next 48 hrs.

We reassess criteria for a PST at least once daily after consent is obtained.

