### Detailed Study Methods

#### Pressure Support Trials

PSTs are required to identify patients at the onset of the recovery phase when patients are first able to tolerate assisted ventilation. We adjust the level of pressure support provided to obtain a RR ≤ 35 breaths/min during PSTs. The initial level of pressure support is set at 15 cm H_2_O for patients not already on this mode and at the current level of pressure support in patients already on pressure support. PSTs are at least 60 consecutive minutes and not longer than 120 minutes in duration. The maximal pressure support (above PEEP) is 22 cm H_2_O and the minimum is 10 cm H_2_O. A PST can be stopped at any time for sustained hemodynamic or respiratory distress (heart rate ≤ 50 or ≥ 140 beats per minute or new significant dysrhythmias, systolic blood pressure ≤ 80 mm Hg or ≥ 180 mm Hg or RR > 40 breaths/min).

A PST is considered successful if after 60 consecutive minutes without a change in the level of pressure support, the patient remains clinically stable with a RR less than or equal to 35 and greater than 10 breaths/min with no decrease in pulse oximetry saturations (SpO_2 _remains ≥ 90% on an FiO_2 _≤ 50% with PEEP ≤ 8 cm H_2_O). Patients who fail a PST are returned to their previous ventilator settings or settings that restore respiratory comfort. We reassess these patients at least daily for criteria to undergo a PST. Patients who *successfully *complete a PST are assessed for a SBT. Patients who do not meet SBT criteria (i.e., are too early to undergo a SBT) are randomized upon successful completion of a PST.

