##### d) Criteria to suspend weaning protocols/return to an alternate mode of ventilation

In both groups, patients are permitted to return to or remain on alternate modes of ventilation for: (i) surgery or invasive procedures requiring sedation, (ii) respiratory distress defined by a) sustained hypoxemia (SpO_2 _< 90%) with FiO_2 _> 60% and PEEP > 10 cm H_2_O or hypercapnia with pH < 7.30 or clinical respiratory distress, b) repeated episodes (≥ 3 episodes within 1 hour wherein an inspiratory pressure (pressure support + PEEP) of 35 cmH_2_O is attained (despite suctioning, bronchodilation etc.), (iii) hemodynamic instability despite fluid boluses and the requirement for high dose vasopressors: norepinephrine > 15µg/min (0.2µg/kg/min) or equivalent, (iv) suspected myocardial ischemia based on electrocardiogram and/or elevated Troponin i, (v) neurologic deterioration with need to control PaCO_2 _(both groups) or alarm indicating "Central hypoventilation" (Automated Weaning), (vi) a requirement for increased sedation resulting in RR < 10 breaths/min. Patients meeting a criterion, are reassessed at least daily with PSTs to identify the earliest time when weaning can be resumed according to the assigned treatment. However, the pre-randomization requirement to undergo a SBT (if criteria are present) is not required at this time point.

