#### Data Collection

We collect data at ICU admission, study inclusion and daily thereafter. Whereas protocol violations (non compliance) in the Automated Weaning arm include return to/remain on an alternate mode of mechanical ventilation in the absence of meeting criteria and any unauthorized interruptions (cessations, manual increases/decreases) in the automated protocol, violations in the Protocolized Weaning group include unauthorized use of modes other than pressure support (i.e., assist control) without criteria to return to or remain on an alternate mode of mechanical ventilation. We tabulate a daily score reflecting the number of SBTs conducted divided by the number of required SBT assessments in which all criteria were met in the Protocolized Weaning group. Sedation protocol compliance is assessed by the percentage of daily SAS scores < 2 or > 5 (or alternatively, RASS scores < - 4 or > +1) in both arms. We also evaluate compliance with the PEEP/FiO_2 _chart in both groups. RRT and physician acceptance of the weaning protocols and critical care nurse acceptance of the sedation protocol is assessed daily using Likert [40] scales [ranging from 0 highly unacceptable (extremely difficult to use) to 10 highly acceptable (extremely easy to use)].

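### Read literally, the weaning-compliance rule in the primary outcome scores as violations some hours in which staff are waiting for, barred from, or have just failed the Pressure Support Trial that leads back to weaning

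*Protocol article*

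**What the plan says.** All references are to the protocol article.

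- **Violation rule (Statistical Analyses).** The weaning part of the primary outcome counts "protocol violations (off protocol hours without meeting criteria to return to/remain on an alternate mode of mechanical ventilation". The acceptance rule is "Compliance will be considered acceptable if ≥ 75" per cent, so violations must stay below 25% of the time. The summary is by arm: "We will evaluate the percentage of (i) hours off-protocol and (ii) daily SAS scores < 2 or > 5 (or RASS equivalent) by treatment group".
- **Violation by arm (Data Collection).** In the Automated arm it includes "return to/remain on an alternate mode of mechanical ventilation in the absence of meeting criteria", and also unauthorised interruptions of the automated protocol. In the Protocolized arm it is "unauthorized use of modes other than pressure support (i.e., assist control) without criteria to return to or remain on an alternate mode".
- **Suspension list (section d, Criteria to suspend weaning protocols).** A single list, items (i) to (vi), covers both going back to an alternate mode and staying on one.
- **Route back (same section).** Patients who meet a criterion are "reassessed at least daily with PSTs to identify the earliest time when weaning can be resumed". Only the spontaneous breathing trial is waived.
- **PST entry (Criteria for Pressure Support Trial).** Conditions include oxygenation limits, 24 h without neurological deterioration, and "no surgery or procedure requiring sedation planned in the next 48 hrs".
- **Failed PST (Pressure Support Trials).** "Patients who fail a PST are returned to their previous ventilator settings or settings that restore respiratory comfort", with reassessment at least daily.

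**The concern.** The rule that authorises time off protocol and the rule that brings a patient back to weaning do not share an endpoint. Authorisation depends on a listed criterion being met, while return depends on a PST. A patient can be past the first and not yet through the second. In that interval staff are following the suspension section, but the violation rule, taken word for word, has no category that excuses the hours.

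The error runs in one direction: it can only lower measured compliance. Compliance is the primary outcome and a main basis for judging whether a definitive trial is feasible. Hours misclassified in this way use up part of the 25% allowance meant for real departures. The same records would also give two different values of the primary outcome, depending on which reading the analyst takes.

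**Working it through.** **Step 1. The plan's own figure.** Acceptable compliance is at least 75%, so the violation allowance is 1 − 0.75 = 0.25. No stated number is wrong. The sample size of 90 has no formula behind it to check.

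**Step 2. Thresholds side by side (oxygenation).**

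| Rule | SpO2 | FiO2 | PEEP (cm H2O) |
|---|---|---|---|
| Suspend or stay off protocol | < 90% | > 60% | > 10 |
| Enter a PST | ≥ 90% | ≤ 50% | ≤ 10 |
| Pass a PST | ≥ 90% | ≤ 50% | ≤ 8 |

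Three intervals follow.
- SpO2 92% on FiO2 55% and PEEP 10 meets no oxygenation criterion for staying off protocol, and it does not satisfy PST entry.
- At PEEP 9 or 10 a PST may begin but cannot be judged successful unless PEEP falls. After a failed PST the patient goes back to earlier settings, and a failed PST is not a listed criterion.
- Once a criterion has cleared, the next PST may be up to a day away. This interval arises whatever the PST entry limits are.

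Not every limit differs: the norepinephrine limit is the same in the PST entry criteria and the suspension list.

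**Step 3. Lag per suspension.** Assumptions: one PST per 24 h, a clearing time uniform over the day, and the first PST entered and passed. The PST lasts 60 to 120 min (Pressure Support Trials).
- Mean: 24/2 + 1 = 13 h.
- Maximum: 24 + 1 = 25 h, or 24 + 2 = 26 h with a two-hour PST.
- The lag is longer if a PST is failed or cannot be entered, and shorter if PSTs are done more than once a day.
- In the Protocolized arm the PST itself runs in pressure support, so its hour may not count. The mean lag is then 12 h.

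**Step 4. Share of an affected patient's time.** The share is w/T, where w is the lag and T the hours at risk. The article gives no T for this trial. As an assumption, T is set to the median durations of 4 and 2 days quoted in the Background from an earlier trial, that is 96 h and 48 h.
- T = 96 h: 13/96 = 13.5%; 25/96 = 26.0%; 26/96 = 27.1%.
- T = 48 h: 13/48 = 27.1%; 25/48 = 52.1%; 26/48 = 54.2%.

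**Step 5. Share at arm level.** The share is f × w/T, where f is the proportion of patients suspended once. The documents do not give f.

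| f | T = 96 h, w = 13 to 25 h | T = 48 h, w = 13 to 25 h |
|---|---|---|
| 0.10 | 1.4% to 2.6% | 2.7% to 5.2% |
| 0.25 | 3.4% to 6.5% | 6.8% to 13.0% |
| 0.50 | 6.8% to 13.0% | 13.5% to 26.0% |
| 1.00 | 13.5% to 26.0% | 27.1% to 52.1% |

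With w = 26 h, f = 0.25 and T = 96 h the share is 0.25 × 26/96 = 6.8%. With w = 12 h it is 0.25 × 12/96 = 3.1%. Doubling T halves every entry.

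**Step 6. What would fail an arm.** These hours alone reach the limit only if they average at least 0.25 × 96 = 24 h per patient, or 0.25 × 48 = 12 h with the shorter base.

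**The case against.** **The hour-by-hour reading is an inference.** Nowhere does the article say that an hour becomes a violation when the criterion clears. One can read the suspension section as a criterion opening the suspension and a PST closing it, and waiting under a prescribed procedure is hard to call unauthorised. This stands as a possible reading. It does not dispose of the point. The violation rule refers to meeting criteria for remaining as well as returning, which suggests that a criterion must still hold, and the text settles neither reading.

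**The PST entry list may not govern resumption.** It is written for consented patients before randomisation, and one item refers to the day of randomisation. A passed PST as a condition for resuming is explicit only for reintubation within 48 hours in the Automated arm; elsewhere it is strongly implied. This stands, and it is a reason to state which criteria apply. The wait for the next daily PST and the time after a failed PST do not depend on the entry list.

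**Some cases are already covered.** Surgery or sedated procedures are listed with no end time. Clinical respiratory distress, haemodynamic instability and neurological deterioration would cover some failed PSTs and some neurological cases. This stands and narrows the problem.

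**Detail may be elsewhere.** Additional file 1 and an analysis plan are not shown. But the article itself states the violation rule and its threshold, and describes the weaning-strategy appendices as covering initiation, titration and discontinuation. The difficulty is in a stated rule, not in an omitted detail.

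**Stronger readings.** A reader might infer that sites which follow the protocol are declared non-compliant. The documents do not support that: hours are judged by treatment group, with a 25% allowance. A reader might also infer a bias between arms, because the central hypoventilation alarm exists only in the Automated arm. It sits beside a neurological trigger common to both arms, and no figure shows that suspension is unequal.

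**Conclusion.** The point holds in a limited form. The violation rule and the suspension list make no provision for time awaiting, ineligible for, or following failure of the PST used to return to weaning. Read literally, some protocol-adherent hours are scored as violations, and measured compliance in each arm is biased downward against the 75% limit.

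The size cannot be fixed from the documents. With daily PSTs, 25% of patients suspended once and 96 h at risk, it is roughly 3 to 7 percentage points per arm. Suspension frequency, lag and the 96 h base are all assumptions. The base is a median from another trial; if durations are right-skewed or suspended patients stay at risk longer, the share is smaller. It would be tempting to conclude that the rule makes an arm fail, but that needs an average of 24 h of such time per patient on the 96 h base, and nothing in the article shows it.

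The severity is moderate. The scoring should be settled before the primary outcome is analysed.

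**What to change.** In Data Collection and Statistical Analyses, define off-protocol time as authorised from the first documented suspension criterion until the first passed PST. Within that period count a violation only when:

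- the PST criteria were met and the due daily PST was not done; or
- a PST was passed and the assigned strategy was not resumed.

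Reconcile the Criteria for Pressure Support Trial, Pressure Support Trials and suspension sections by stating which PST criteria apply when weaning is resumed after randomisation. This can be done without altering any clinical threshold.

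The cost is a change of wording, plus confirmation that the case report forms record the times of suspension criteria, PSTs and resumption. The downside is that some real delay in resuming will be detected only through missed PSTs.

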##### f) Sedation titration

We developed a sedation guide to guide sedation administration and limit performance bias during weaning. Critical care nurses titrate sedation to achieve either a Sedation Agitation Scale (SAS) [33] score of 3 to 4 (see Additional file 1, Appendix 3) or a Richmond Agitation Scale Score (RASS) [34] of -3 to 0 [35]. Sedation titration is not mandatory in patients meeting criteria to return to or remain on an alternate mode of ventilation.

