#### Study Outcomes

The primary outcome of the WEAN pilot study is compliance with the weaning and sedation protocols. Secondary outcomes include (i) daytime clinician (nurse; RRT and physician) acceptance of the sedation and weaning protocols, respectively, (ii) time to successful extubation defined as the time from randomization to unsupported (no requirement for NIV or invasive ventilation), spontaneous breathing for ≥ 48 hours after extubation (or disconnection with a tracheostomy), (iii) time to completion of a successful SBT, (iv) total duration of mechanical ventilation (time from intubation to termination of ventilation), (vi) ICU and hospital length of stay, (vii) ICU and hospital mortality, and the proportion of patients (viii) developing nosocomial pneumonia [39], (ix) with weaning (self-extubation, tracheostomy, reintubation and prolonged mechanical ventilation >21 days) or ICU (myocardial infarction and pneumothoraces) complications, and (x) requiring NIV. Any NIV use is considered clinically relevant.

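### The sedation acceptance rule prints its lower RASS limit with the inequality transposed, in conflict with the Data Collection section; a minor slip, but in a primary-outcome threshold

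*Protocol article*

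**What the plan says.** Under Study Outcomes: "The primary outcome of the WEAN pilot study is compliance with the weaning and sedation protocols". Three places in the Methods then bear on how a RASS score is judged.

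- **Sedation titration** (item f of the weaning procedures) lets nurses work to an SAS score of 3 to 4 or to "a Richmond Agitation Scale Score (RASS) [34] of -3 to 0".
- **Data Collection** defines non-compliance as the "percentage of daily SAS scores < 2 or > 5 (or alternatively, RASS scores < - 4 or > +1) in both arms".
- **Statistical Analyses** first announces a summary of "daily SAS scores < 2 or > 5 (or RASS equivalent) by treatment group", without RASS numbers. It then gives the decision rule. That rule begins "Compliance will be considered acceptable if ≥ 75" (per cent) and for sedation is spelled out as "SAS scores < 2 or > 5 (equivalent RASS -4 < or > +1) occur < 25% of the time".

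The SAS limits are identical in the last two sections. The RASS upper limit also agrees. Only the lower RASS limit differs: the less-than sign stands before the -4 in Data Collection and after it in Statistical Analyses.

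**The concern.** Two sections define the same component of the primary outcome, and their lower RASS limits point in opposite directions. The transposed one is in the sentence that turns the data into a verdict of acceptable or not acceptable. It is also the only place in Statistical Analyses where RASS limits appear as numbers, so someone programming from that section alone would find no correct version there.

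What is at stake is the sedation part of the feasibility conclusion, for scores recorded on the RASS. If the expression were coded as printed, on-target sedation would be reported as non-compliance and the deepest score would pass as compliant.

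**Working it through.** **Inputs.** RASS target -3 to 0 and SAS target 3 to 4 (Sedation titration). RASS violation if below -4 or above +1 (Data Collection). RASS violation if -4 < score, or score above +1 (Statistical Analyses, read literally). Acceptable if violations are under 25% (Statistical Analyses). The article does not give the span of the scale. I assume whole scores from -5 to +4; the result for the target range does not depend on this.

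**Step 1: list the violation scores.**

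- Data Collection: -5, +2, +3, +4. None of the four target scores is included.
- Statistical Analyses, literal: -3, -2, -1, 0, +1, +2, +3, +4. All four target scores are included and -5 is not.
- The two lists disagree at -5, -3, -2, -1, 0 and +1. They agree at -4 (not a violation under either) and from +2 upward (a violation under both).
- In the literal version the upper limit adds nothing, since any score above +1 is already above -4.

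**Step 2: compare with the SAS rule, which the sentence calls equivalent.** Around an SAS target of 3 to 4, violations are below 2 or above 5, so 2 and 5 are tolerated: one point on each side. Around a RASS target of -3 to 0, the Data Collection limits tolerate -4 and +1: again one point on each side. The literal Statistical Analyses limits do not have this structure.

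**Step 3: size.** Let a be the share of RASS scores at -5, b the share from -3 to +1, and c the share at +2 or above; the rest are at -4.

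- Violations under Data Collection = a + c.
- Violations under the literal rule = b + c.
- Difference (literal minus Data Collection) = b - a.

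With assumed mixes of scores:

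| Assumed RASS scores | Data Collection | Literal Statistical Analyses | Verdict at 25% |
|---|---|---|---|
| All on target | 0% | 100% | flips |
| 90% on target, 10% at -5 | 10% | 90% | flips |
| 75% on target, 25% at -5 | 25% | 75% | not acceptable under either |
| All at -4 | 0% | 0% | acceptable under either |
| All at -5 | 100% | 0% | flips the other way |

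**Step 4: dilution by SAS data.** Suppose a fraction r of all scores is RASS, the two scales are pooled, and every score is on target. Literal violations are then r × 100% + (1 - r) × 0% = r. The pooled figure stays under 25% if r is below 25% and reaches the limit at r = 25%. The article gives no value for r, so the effect in this example runs from nil (r = 0) to 100% (r = 1).

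**The case against.** The strongest reply is that this is a misplaced symbol and that the document corrects it. Data Collection prints the limit the other way round. The disputed bracket calls itself equivalent to a two-sided SAS rule, which the literal version is not. A rule that makes every target score a violation is visibly unintended. The expression is also malformed: nothing follows the less-than sign, so the reader must supply the variable to reach the literal reading. All of this stands, and it is why the point is minor.

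A reader might go further and infer that the plan's feasibility verdict would reverse, or that over-sedation would go uncounted. The documents do not support either claim. A reversal needs an analyst to code the malformed expression literally, against Data Collection and the stated target, and to accept the result. Even then it touches RASS-scored data only, and a change in the overall verdict depends on a RASS share that is not stated. On the deep side, -4 is compliant under both versions; on the assumed scale the rules differ there only at -5.

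The reply does not show that the text is right. That the intent can be recovered lowers the chance of harm, but the two sections still contradict each other on a threshold for the primary outcome.

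**Conclusion.** The contradiction is real and the expression in Statistical Analyses is wrong as printed. It is very probably typographical, and the article's own text shows which version was meant: the Data Collection limits fit the target range, match the structure of the SAS limits and leave both halves of the rule doing some work.

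The consequence is conditional. If the rule is programmed literally, a patient always on target moves from 0% to 100% violations, and the verdict against 25% can flip for RASS-scored data. If the analyst follows Data Collection, nothing changes. SAS-scored data are unaffected in either case, and the sample size of 90 was not derived from this threshold. The mixes of scores used above are assumptions that show the mechanism; they are not estimates for this trial. Severity: minor.

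**What to change.** In the acceptance rule in Statistical Analyses, replace the bracketed RASS limits with those of Data Collection, "RASS scores < - 4 or > +1". Confirm that the analysis program and the compliance report use that single rule for every RASS score. This changes how compliance is scored on paper and leaves the sedation target and bedside procedure as they are. The cost is one corrected expression and one check of the code, with no extra data, patients or procedures.
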